**Project indicators**

Effectiveness will be measured by comparing quantitative health impact indicators for TB and HIV over the implementation period of Triage-Plus. The demographic and health survey (DHS) report of 2004 used the following defining characteristics and impact indicators: basic population; age composition and structure; gender, level of education, TB, HIV and poverty prevalence. Other indicators will be the number of cases identified, the proportion of cases put on single treatment and the proportion cases put on dual treatment. The same impact indicators will be measured in this study at baseline and on- going till the end of the project in both clusters (i.e. where Triage-Plus is and is not implemented). In this way the intervention is both historically and concurrently controlled.

There is a strong recognition that Triage-Plus is, however, a health system intervention, not a new drug. Therefore the methodology incorporates adaptations and additions to the clinical trial approach such as health economics and qualitative process evaluation. The former to analyse the cost effectiveness of the intervention to patients, informal healthcare providers and the formal health system and the latter to document the multiple changes, processes and to provide the context for the trial findings. In addition, an overarching strategy for the whole research process will be continuous involvement of the research partners, participation of the communities involved in the research, and engagement of those who need and will use the research results.

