| 305 | Who decided that you should go there? |  | 1. Self 2. Spouse 3. Household head 4. Relatives/friends 5. Employer 6. Storekeeper referred 7. Referral health worker 8. Othersp:_______   99. Not known | DECIDE |  |  |  |  |  |  |  |  |  |  |
| 306 | a) Did you go there with a guardian? | *If No go to 307* | 1.Yes  2.No |  |  |  |  |  |  |  |  |  |  |  |
|  | b**)** If yes specify the sex of the guardian |  |  | GUARD1 |  |  |  |  |  |  |  |  |  |  |
| 1.Male  2.Female |  |  |
| 307 | How much did you spend (on drugs, fees, consultation)? | *Fill in for each visit to the care provider* | MK | FEES1 | MK | MK | MK | MK | MK | MK | MK | MK | MK | MK |
| 308 | How did you get the money? |  | 1.Own money  2. From Spouse  3.From children/parents  4.From friends/relatives  5.Borrowed (without interest)  6.Borrowed (with interest)  7.Begging  8.Sold assets  9.Othersp:__________ | MONEYHOS |  |  |  |  |  |  |  |  |  |  |

|  |  |  |  |  | 1st | 2nd | 3rd | 4th | 5th | 6th | 7th | 8th | 9th | 10th |
| --- | --- | --- | --- | --- | --- | --- | --- | --- | --- | --- | --- | --- | --- | --- |
| 309 | How did you travel? |  | 1. Did not travel | TPTMODE1 |  |  |  |  |  |  |  |  |  |  |
| 2. Walk | TPTMODE2 |  |  |  |  |  |  |  |  |  |  |
| 3. Bus/Minibus | TPTMODE3 |  |  |  |  |  |  |  |  |  |  |
| 4. Ambulance | TPTMODE4 |  |  |  |  |  |  |  |  |  |  |
| 5 Bicycle | TPTMODE5 |  |  |  |  |  |  |  |  |  |  |
| 6 Own car | TPTMODE6 |  |  |  |  |  |  |  |  |  |  |
| 7 Hired car/Taxi/bicycle | TPTMODE7 |  |  |  |  |  |  |  |  |  |  |
| 8. Stretcher | TPTMODE8 |  |  |  |  |  |  |  |  |  |  |
| 9. Wheel barrow/Oxcart | TPTMODE9 |  |  |  |  |  |  |  |  |  |  |
| 10. Other sp: | TPTMODE10 |  |  |  |  |  |  |  |  |  |  |
| 99. Not Known |  |  |  |  |  |  |  |  |  |  |  |
| 310 | How much did you pay for transport (going there and back including for guardian(s))? | *Fill in for each visit to the care provider*  *(if answer is 2 above then skip this question)* | MK | TPTCOST1 | MK | MK | MK | MK | MK | MK | MK | MK | MK | MK |
| 311 | How much time did you take to go and come back (hrs)? | *Fill in for each visit to the care provider* | Hours | TIME1 | HRS | HRS | HRS | HRS | HRS | HRS | HRS | HRS | HRS | HRS |
| 312 | How much did you spend on food and incidentals? | *Fill in for each visit to the care provider* | MK | FOODFEE1 | MK | MK | MK | MK | MK | MK | MK | MK | MK | MK |

|  |  | | |  | |  | |  | 1st | 2nd | 3rd | 4th | 5th | 6th | 7th | 8th | 9th | 10th | |

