| --- | --- | --- | --- | --- | --- | --- | --- | --- | --- | --- | --- | --- | --- | --- | --- | --- | --- | --- | --- |
| 313 | How did you get the money to pay for food, incidentals and transport? | | |  | | 1. Own money | | MONEY1 |  |  |  |  |  |  |  |  |  |  | |
| 2. From spouse (gift) | |  |  |  |  |  |  |  |  |  |  | |
| 3. From children/parents (gift) | |  |  |  |  |  |  |  |  |  |  | |
| 4. From friends/relatives (gift) | |  |  |  |  |  |  |  |  |  |  | |
| 5. Borrowed (without interest) | |  |  |  |  |  |  |  |  |  |  | |
| 6. Borrowed (with interest) | |  |  |  |  |  |  |  |  |  |  | |
| 7. Begging | |  |  |  |  |  |  |  |  |  |  | |
| 8. Sold asset | |  |  |  |  |  |  |  |  |  |  | |
| 9. Other sp: ____________________ | |  |  |  |  |  |  |  |  |  |  | |
| 99. Not known | |  |  |  |  |  |  |  |  |  |  | |
| 314 | Total spent at each care provider? | | | *Calculate sum spent seeking care from each care provider (****for interviewer)*** | | MK | | TOTAL1 | MK | MK | MK | MK | MK | MK | MK | MK | MK | MK | |
|  | |  |  |  |  |  |  |  |  |  |  | |
| 315 | Did you submit sputum? | | | *Fill in for each visit to the care provider* | | 1. Yes | | SPUTUM1 |  |  |  |  |  |  |  |  |  |  | |
| 2. No | |  |  |  |  |  |  |  |  |  |  | |
| 316 | When did you submit sputum? | | | *Enter month in figures* | | Date Month Year | | DATSPU |  |  |  |  |  |  |  |  |  |  | |
| 317 | When did you get results? | | | *Enter month in figures* | | Date Month Year | | DATERES |  |  |  |  |  |  |  |  |  |  | |
| 318 | What was the result of the sputum exam? | | | *Fill in for each visit to the care provider* | | 1. Nothing wrong | | RESULT1 |  |  |  |  |  |  |  |  |  |  | |
| 2. Negative | |  |  |  |  |  |  |  |  |  |  | |
| 3. Positive | |  |  |  |  |  |  |  |  |  |  | |
| 4. No result | |  |  |  |  |  |  |  |  |  |  | |
| 99. Don't know | |  |  |  |  |  |  |  |  |  |  | |
| 319 | | Did you get tested for HIV |  | | 1. Yes 2. No | |  | | | | | | | | | | | |  |
| 320 | | When did you get tested |  | | Day month year | |  | | | | | | | | | | | |  |
| 321 | | What was the result of the test |  | | 1. Positive 2. Negative 3. Don’t know | |  | | | | | | | | | | | |  |

|  |  |  |  |  |
| --- | --- | --- | --- | --- |
| 401 | How many days have you lost work whilst getting a diagnosis for TB? | *Enter days in figures* | _____ | LOSTWORK |
| 402 | How many days have you lost work whilst seeking an HIV test |  |  | LOSTWORK1 |

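### The skip on the transport-fare item depends only on how the patient travelled, although the item also covers the return leg and guardians, so some fares may never be asked

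*Protocol*

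**What the plan says.** All the items concerned are in Protocol, Appendix 4 (Survey questionnaire).

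- Item 309 asks "How did you travel" for each step of the care pathway. Each mode has its own variable, among them "1. Did not travel | TPTMODE1" and "2. Walk | TPTMODE2".
- Item 310 asks "How much did you pay for transport (going there and back including for guardian(s" and is to be completed for each visit. It carries the instruction "if answer is 2 above then skip this question".
- Item 306 asks "a) Did you go there with a guardian". The skip on item 310 does not refer to this answer.
- Item 314 is worked out by the interviewer: "Calculate sum spent seeking care from each care provider".

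The section on data collection tools for the health economic evaluation names this questionnaire as the patient survey, run at the beginning of the intervention and at the end of the trial. Project indicators gives one purpose of the economic work as "to analyse the cost effectiveness of the intervention to patients", and cost-effectiveness is also listed under Objectives.

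**The concern.** The condition for skipping item 310 is narrower than the question being skipped. The condition concerns one person's mode of travel. The question concerns money paid for two legs and possibly for more than one person. When the two come apart, a real payment is not recorded.

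Transport is a patient cost that the intervention is expected to change: under Potential benefits the protocol predicts lower costs of access because services move into the communities. Appendix 4 is the only patient-cost instrument shown. A fare that was never asked cannot be restored at the analysis stage, whatever the analysis plan says about missing values.

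**Working it through.** The protocol states no fare, no share of walked trips and no transport total, so there is no figure to reproduce. The check is a reading of items 306 to 314 together, by type of trip.

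| Trip | Code at 309 | Item 310 | Effect on 314 |
|---|---|---|---|
| Walked both ways, nobody paid | 2 | skipped | none; true fare is 0 |
| Walked one leg, paid on the other, marked Walk only | 2 | skipped | fare lost |
| Same trip, both modes marked | 2 and 3 | skip condition literally met, but no rule for two codes | depends on the interviewer |
| Same trip, paid mode marked only | 3 | asked | fare captured |
| Patient walked, guardian's fare paid | 2 | skipped | fare lost |
| Did not travel | 1 | asked | MK 0 can be entered |

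**Can a lost fare be recovered?** No. Item 307 covers drugs, fees and consultation. Item 312 covers food and incidentals. Item 313 asks where the money for food, incidentals and transport came from, but takes no amount. Items 306 and 309 can flag a trip at risk but cannot supply the sum.

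**Illustration of size, on assumptions only.** Let w be the share of trips coded Walk and m the share of those with one paid leg at half the round-trip fare. All other trips pay the full fare, set to 1, and skipped items count as 0.

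- True mean fare = (1 − w) + wm/2
- Recorded mean fare = 1 − w
- Proportion lost = (wm/2) / [(1 − w) + wm/2]

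Results:

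- w = 0.2, m = 0.05: 0.005 / 0.805 = 0.6%
- w = 0.5, m = 0.10: 0.025 / 0.525 = 4.8%
- w = 0.8, m = 0.20: 0.080 / 0.280 = 28.6%

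With m = 0 the loss is zero at every w. The range shows only that the size depends on quantities that the protocol does not give.

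**Effect on a comparison.** If the mean hidden fare per trip is h1 in one group or survey round and h0 in the other, the absolute difference in recorded mean cost is off by −(h1 − h0). It is unbiased when h1 = h0. Walking may become more common as services move closer, in which case the two could differ, but the documents give no basis for saying by how much.

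**The case against.** Four objections deserve an answer.

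1. **Part-walked trips need not be coded Walk alone.** Item 309 has one variable per mode. Unlike items 204 and 205, it does not restrict the answer to a single choice. Someone who walked to the bus stage may well answer bus, and item 310 is then asked. This stands: loss on such trips is possible, not certain. It does not rescue the rule, because with two codes marked the skip condition is still literally met and nothing tells the interviewer what to do. It also does not reach the guardian's fare, since a walking patient is correctly coded 2 alone.

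2. **A patient who walks while a guardian rides is unusual.** Item 306 concerns a guardian who went along. This is fair and limits the likely frequency of that case. It leaves the patient who walked one leg and paid for the other.

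3. **Blanks on walked trips are harmless.** A reader might infer that leaving item 310 blank on a free walked trip, while a patient who did not travel can receive MK 0, corrupts the costs. The documents do not support this. The blank is identifiable as a structural zero from the Walk code and adds nothing at item 314. It would distort a mean only if an analyst dropped it as missing. With m = 0, that would inflate the mean by 1/(1 − w), a factor of 2 at w = 0.5. The protocol nowhere proposes this, and such handling properly belongs to an analysis plan that is not shown.

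4. **The primary outcomes are untouched.** This stands in full. Numbers starting TB treatment and ART come from audited registers.

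**Conclusion.** The skip rule does not match the scope of the item it suppresses. Fares for a second leg, for a guardian, or on a part-walked trip marked Walk can go unrecorded, drop out of the provider total and be lost for good. Any resulting error in transport cost is an understatement when the skipped item counts as zero.

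A reader might conclude that the patient costs are wrong, or that the difference in cost between groups must be biased. Neither follows. The first needs a material share of walk-coded trips with a hidden fare; the second needs the mean hidden fare to differ between the groups or rounds compared. The documents give no information on either, and the percentages above rest wholly on assumed shares.

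This is a minor point of form design, confined to one component of patient cost in the economic evaluation. It is worth correcting because the loss cannot be repaired after the interview.

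**What to change.** Before the first survey round:

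- Delete the skip and ask item 310 for every visit.
- Instruct the interviewer at item 309 to mark all modes used on both legs.
- Enter MK 0 at item 310 when neither the patient nor a guardian paid for either leg.
- Give an unknown fare a distinct non-numeric code and keep it out of the sum at item 314. The form's usual 99 should not be used here, because in a money field it reads as MK 99 and could be added into the total.

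The cost is a small edit to the form and interviewer instructions, plus a few seconds per visit in the interview.
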